**6. SPECIFIC AIMS**

Authoritative parenting style has been associated with decreased obesity risk in children and can modify the delivery and impact of weight control strategies, making them more effective. At this time, gold-standard treatment for childhood obesity is family-based behavioral therapy (FBT). This treatment relies on behavioral strategies and the use of praise and a positive reinforcement system to change eating and activity behaviors, but does not target other aspects of parenting. Broadening parenting instruction to include effective limit-setting behaviors, parent-child communication, and authoritative parenting may increase parents' confidence and ability to successfully make behavior changes and modify the impact of the behavioral strategies being used.

In this application, we propose to test the efficacy of a 6 month, 20-sessions, weight control program that combines traditional family-based behavioral therapy with comprehensive parenting training (FBT+PT) and compare it to traditional family-based behavioral therapy (FBT). The FBT+PT arm will incorporate more active

skills learning to increase adoption of authoritative parenting behaviors. We will recruit and randomize 160 overweight/obese children (BMI>85th percentile and <99.9th percentile) between 7 and 12 years old and their parent into a 6 month, 20-sessions FBT+PT or FBT program and follow them for 1 year post-treatment. The primary outcome is change in child body weight (BMI z-score). Our secondary aim will be to evaluate the effect of both treatments on drop-out rates, adherence, and acceptability. As an exploratory aim, we will evaluate parent and child level mediators and moderators of weight loss in each of the treatment arms in order to inform future treatment development. We will achieve the goals of this application by pursuing the following primary and secondary aims:

- **Primary aim 1:** Examine the efficacy of FBT+PT on child body weight compared to gold standard FBT. *We hypothesize that FBT+PT will show greater decreases in child body weight (BMI z-score) compared to FBT at post-treatment and 6- and 12-months post-treatment.*
- **Secondary aim 1:** Examine drop-out, treatment adherence, and acceptability in FBT+PT and FBT. We hypothesize that families randomized to FBT+PT will have lower drop-out rates, increased program adherence (including attendance, self-monitoring, use of praise), and higher ratings of acceptability.

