- **Exploratory aim:** Examine mediators and moderators of weight loss in FBT+PT and FBT. We hypothesize that success will be *mediated* by actual change in parenting and behavioral skills, as well as self-efficacy to engage in behavior change. We propose that a) increased parent use of praise, b) effective limit-setting, c) decreased use of harsh parenting techniques, and d) increased behavior change self-efficacy will *mediate* the impact of the intervention on child weight status. We also hypothesize that a) sociodemographic factors (race/ethnicity, income, and education), b) baseline general parenting style, c) parent mental health status, and d) child responsivity to food cues will *moderate* treatment effects. Several factors (e.g., family functioning, chaos level, and child internalizing/externalizing behaviors) may act as both mediators and moderators of treatment effect and will be tested in both capacities.

In September 2017, we received an ancillary grant (R01DK114794), to examine reward and inhibition aspects of cognition, in both parents and children enrolled in this study (R01DK108686), in order to understand the factors that contribute to lack of response in family-based behavioral weight loss. The primary aims of the ancillary study are to determine behavioral and psychological phenotypes of reward and inhibition at baseline in parents and children and to evaluate whether the behavioral and psychological phenotypes at baseline predict weight loss in both parents and children at the 6-, 12- and 18-month timepoints. An exploratory aim is to evaluate whether the behavioral and psychological phenotypes identified at baseline in parents and children change over the measurement period and whether these changes are associated with weight loss.

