## 7. BACKGROUND AND SIGNIFICANCE

The current gold standard treatment for childhood obesity is family-based behavioral therapy (FBT). This program provides the basic building blocks for weight management, including behavior therapy skills and nutrition and physical activity (PA) education. Children in these programs have shown a mean BMI z-score change of -10.3% (S.D. 9.2). However, not all children respond similarly to FBT, with only about a third of children able to maintain their weight loss over a ten year period. In addition, programs are often plagued by high drop-out rates, from 20% in academic research settings to 70% in clinical settings, impacting their efficacy. Therefore, studies are needed to determine how to optimize FBT for a greater proportion of families.

Cohort studies suggest that authoritative parenting, characterized by greater warmth/attachment and firm limit-setting, is associated with better weight outcomes. This authoritative parenting style may be important because it can alter the context in which behavioral strategies are implemented, thereby making them more effective. Furthermore, the use of praise has been associated with greater weight loss in the context of FBT, while permissive parenting is associated with poorer weight loss outcomes. Current FBT relies on behavioral strategies like self-monitoring, stimulus control, and problem-solving, but offers limited instruction on parenting, focusing only on the use of praise and positive reinforcement. Adding more comprehensive parenting training (that includes limit setting strategies and parent child communication skills) to FBT may increase the effectiveness of these programs. Ultimately, parents may become more confident to deliver weight control strategies and be able to do so in a more effective manner.

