## Analysis:

Analyses will be based on linear mixed models implemented in R statistical software and Mplus v 6.12. Primary outcomes evaluation first will follow an Intention to Treat principle with all missing values presumed returned to baseline level. Planned covariates for primary outcome, change in BMI z-score, will include gender, ethnicity, and parent marital status. For models evaluating the Primary Aim, fixed effects will include coefficients for time, treatment, and time by treatment interactions. For each outcome, selection of a covariance structure for the residuals will be based on fitting different structures (e.g., compound symmetry, unstructured) and selecting the one with the lowest sample size adjusted Akaike's Information Criterion. Significance tests will focus on the treatment by time interactions.

We will conduct analyses examining patient and therapist ratings of treatment acceptability and whether participants believe that the FBT+PT or FBT components address issues that are particularly relevant to them given the level of child behavioral problems. These analyses for the Secondary Aim will be conducted using regressions comparing FBT+PT to FBT. Survival analysis will assess the effect of FBT+PT on decreased risk for treatment drop-out (defined as subject refusal to continue treatment or failing to return to treatment without notification). Planned covariates in survival models will mirror primary analyses. Exploratory analyses will include use of generalized linear mixed effects models for repeated assessments of limited categorical and binary outcomes reflecting energy balance, video tape data, parenting, feeding/lifestyle behaviors, and psychosocial factors.

A multiple-mediator model will provide a test of whether FBT+PT leads to greater changes than FBT on proposed mediators ('a' paths) and whether changes in mediators (e.g., use of praise, limit-setting, problem-

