solving, self-monitoring) at the end of treatment are related to greater decreases in BMIz over time ('b' paths) (Exploratory Aim). The product of these sets of coefficients and associated standard errors will provide effects used to test statistical significance. Mplus 6.12 includes both normal theory and bootstrap methods for estimating both total indirect (all mediators) and specific indirect effects for each proposed mediator. For the moderator hypotheses tested as part of the Exploratory Aim, the models used for the primary aim will be augmented by including a coefficient for the main effect of the moderator (e.g., parent mental health, baseline general parenting style, child food-cue responsiveness) and interactions with treatment and time.

For the Ancillary study:

**Primary aim 1: To determine behavioral and psychological phenotypes of reward and inhibition at baseline in parents and children:** Latent Profile Analysis (LPA) will be used to derive empirically defined groupings of participants based on common patterns of responses to hypothesized inhibitory control (behavioral motor, emotional regulation, and memory for food), reward function (normed physiologic reactivity, self-reported reward responsiveness), and cognitive bias (attentional bias, Stroop bias) indices of risk via maximum likelihood estimation. Models will be estimated with numbers of classes determined iteratively using the Lo-Mendell-Rubin Adjusted Likelihood Ratio Test (LMRT), the Bootstrapped Likelihood Ratio Test (BLRT), Akaike information criteria (AIC), and sample size-adjusted Bayesian information criteria (BIC). In addition to these indices, each model will be evaluated using interpretability of identified conditional means to protect from spurious classes based upon nonnormal distributions.

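### Exploratory mediation: judging the indirect effect by the product of coefficients over its standard error is conservative and can cost up to about 22 points of power; the percentile-bootstrap interval should be named as the test

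*Protocol*

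**What the plan says.** Section 6 (Specific Aims) lists mediation under the exploratory aim: "We hypothesize that success will be *mediated* by actual change in parenting and behavioral skills, as well as self-efficacy to engage in behavior change". The named candidates are praise, limit-setting, less harsh parenting and behaviour-change self-efficacy.

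Section 9 (Analysis) describes a multiple-mediator model. The a paths are the arm differences in change on the mediators. The b paths ask whether mediator changes "at the end of treatment are related to greater decreases in BMI" z-score over time. The product of the two sets of coefficients, with its standard errors, "will provide effects used to test statistical significance". The next sentence reads: "Mplus 6.12 includes both normal theory and bootstrap methods for estimating both total indirect (all mediators) and specific indirect effects for each proposed mediator".

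The section does not say which of the two methods decides significance. It gives no path size, alpha or power for mediation.

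**The concern.** A product of two estimated coefficients is not close to normal when either path is zero or only a few standard errors from zero. Dividing it by a standard error and comparing the ratio with 1.96 then rejects less often than the nominal 5% under no mediation, and loses power when mediation is real.

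Section 6 says this aim is meant to inform future treatment development, and the trial randomises 160 dyads. Power for indirect effects is limited at that size. An avoidable loss makes it more likely that a mediator worth pursuing is passed over.

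**Working it through.** **Inputs from the protocol.** Sample size: "We will recruit and randomize 160 overweight/obese children" (Section 6). A reduced case of 0.80 × 160 = 128 uses the lower background figure in Section 7: "high drop-out rates, from 20% in academic research settings to 70% in clinical settings". The plan has no mediation power figure to reproduce.

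**Assumptions.** Two-sided 5%; 1:1 allocation (the ratio is not stated); one mediator with unit error SD; one outcome time; outcome error variance 1 − b²; no direct effect; independent normal errors. Here a is the arm difference in mediator SD units and b is the slope of outcome on mediator.

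**Why product over SE is conservative.** Write Za = a/SE(a) and Zb = b/SE(b), using the estimates. The first-order statistic is

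z = ab / √(a²·SE(b)² + b²·SE(a)²) = Za·Zb / √(Za² + Zb²).

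If Za = Zb, then z = Za/√2. Both paths must therefore reach 1.96 × 1.414 = 2.77 before the product is declared significant.

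**Large-sample check.** For N = 160, a = 0.4, b = 0.2:
- SE(a) = √(4/160) = 0.158, so the expected Za is 0.4/0.158 = 2.5.
- SE(b) ≈ √(0.96/160) = 0.0775, so the expected Zb is 0.2/0.0775 = 2.6.

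With both expected values at 2.5, simulating the two Z statistics (4,000 replicates) gives power of 27% for product over SE and 47% for percentile limits of the product.

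**Finite-sample simulation** (1,500 trials, 400 resamples; rejection rates in %):

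| N | a | b | Product/SE | Percentile bootstrap | Difference |
|---|---|---|---|---|---|
| 160 | 0 | 0 | 0.1 | 0.1 | 0.0 |
| 160 | 0 | 0.30 | 2.1 | 4.9 | 2.8 |
| 160 | 0.5 | 0 | 1.2 | 4.3 | 3.1 |
| 160 | 0.2 | 0.14 | 1.7 | 8.2 | 6.5 |
| 160 | 0.4 | 0.20 | 29.1 | 50.8 | 21.7 |
| 160 | 0.45 | 0.22 | 41.7 | 62.2 | 20.5 |
| 160 | 0.5 | 0.25 | 61.3 | 78.1 | 16.8 |
| 160 | 0.6 | 0.30 | 88.2 | 93.9 | 5.7 |
| 160 | 0.8 | 0.30 | 96.7 | 97.5 | 0.8 |
| 128 | 0.45 | 0.22 | 28.1 | 50.1 | 22.0 |
| 128 | 0.5 | 0.25 | 43.7 | 64.6 | 20.9 |
| 128 | 0.8 | 0.30 | 89.1 | 93.6 | 4.5 |

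Repeat runs of N = 160, a = 0.4, b = 0.2 gave 27% to 28% against 49% to 50%.

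**Does a bootstrap standard error help?** No (N = 160, 4,000 trials, 400 resamples; %):

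| a | b | Product / normal-theory SE | Product / bootstrap SE | Percentile interval |
|---|---|---|---|---|
| 0.5 | 0 | 1.0 | 1.0 | 4.4 |
| 0.4 | 0.20 | 27.8 | 26.5 | 49.1 |
| 0.45 | 0.22 | 43.4 | 40.4 | 63.3 |
| 0.5 | 0.25 | 61.3 | 57.6 | 78.3 |

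**Which bootstrap interval?** With one path zero, the bias-corrected interval rejected 7.6% to 7.7% at N = 160 and 8.6% at N = 128, against 4.3% to 5.2% for the percentile interval.

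**More than one mediator.** With four mediators correlated at 0.3 (600 trials), power for a specific indirect effect was 53% against 73% at N = 160 (a = 0.5, b = 0.25), and 49% against 68% at N = 128 (a = 0.5, b = 0.3).

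**The case against.** The strongest reply is that the protocol does not choose the normal-theory test. It names the bootstrap in the next sentence, states no 1.96 rule and writes down no null hypothesis for the product. Choosing between two named methods for an exploratory model is ordinary analysis-plan detail, and such a plan may exist. The reference numbers given for the product and its standard errors (22 and 19) lead in Section 22 to videotape parent-training studies, so the intended standard error cannot be traced.

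Much of this stands, and it rules out three stronger readings:
- A reader might infer that the trial will use the normal-theory test. The text does not say so; the loss arises only if product over standard error decides.
- A reader might infer that naming two methods leaves the team free to pick the better result afterwards. That rests on silence which a statistical analysis plan could fill.
- A reader might infer a general loss of about 20 points. That is near the maximum under assumed path sizes. The difference falls to about 1 to 7 points when both paths are strong or both weak.

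It is also fair that the error is in the conservative direction, so it creates no false mediators, and that joint significance of the two paths performs about as well as the percentile interval (52.5% against 50.8% at N = 160, a = 0.4, b = 0.2).

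The reply does not remove the point. The protocol is not merely silent: it states that the product and its standard errors are what significance is tested with. Taken at its word, that gives the weaker test, whichever of the two methods supplies the standard error.

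**Conclusion.** The point holds as an optional improvement to an exploratory analysis. If product over standard error against a normal reference decides, the test rejects about 1% to 2% when exactly one path is zero. At 160 dyads it gives up from about 1 to about 22 points of power against a percentile-bootstrap interval, and about 22 points at most at 128. The loss is greatest when both paths are moderate and similarly precise. When both paths are zero, both methods reject 0.3% or less, so the bootstrap has no practical advantage there.

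These figures depend on assumed path sizes and a simplified model. Repeated BMI z-scores and group delivery of treatment would change the exact numbers, and the total indirect effect was not simulated. The primary comparison of BMI z-score is not affected.

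**What to change.** In Section 9 (Analysis), replace the statement that the product and its standard errors test significance with one sentence: total and specific indirect effects are judged by the percentile-bootstrap 95% confidence interval (for example 5,000 resamples), and not by the product over a normal-theory or bootstrap standard error.

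The sentence should name the percentile interval. A general reference to the bootstrap would still allow product over bootstrap standard error, which recovers nothing, or the bias-corrected interval, whose type I error can reach about 8% to 9%.

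The cost is that sentence and some computing time. The protocol already lists bootstrap methods as part of its software. If the team intended this interval all along, saying so costs nothing further.

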### **Measures:**

Data from the child and the parent will be obtained specifically for research purposes. Data will be collected at 4 time points (baseline, post-treatment (6 months), and 6- and 12-months post-treatment). Assessments will be completed either in-person at the CHEAR office or in a password protected ZOOM meeting. The baseline assessment will include 3 approximately three-hour visits for the child and parent. At the baseline assessment, parents and children will complete surveys and be weighed and measured. Children will also wear an accelerometer for 7 days. Parents and children will be scheduled to complete a videotape family meal at their home. Following the first assessment visit, parents will be given the option of completing some surveys via the secure-web-based survey format prior to attending the in-person visit to reduce the amount of time they need to be present at CHEAR. If parents do not complete the surveys in advance, they will complete them as part of the visit. All surveys provided to be completed at home will include information that does not warrant immediate follow-up (i.e., no questions about suicidal ideation or self-harm). All surveys will be identified with the unique study ID rather than any identifying information. The assessments at follow-up time points (post-treatment (6 months), and 6- and 12-months post-treatment) will be similar to the baseline assessments and will consist of 2 approximately three-hour visits for the child and parent. In addition, families be offered the option of one additional assessment visit (similar to baseline) at post-treatment (6 months), and 6- and 12-months post-treatment, in order to evaluate the aims of the ancillary study. This visit will involve an additional consent form and additional compensation.

Weights will be obtained throughout the treatment program and heights will be obtained at the mid-treatment, post-treatment, and 6- and 12-months post-treatment assessment. The full battery of surveys, accelerometer data, dietary questions, and videotape assessment will occur again at post-treatment and 6- and 12-months post-treatment. A saliva sample for genetic material will only be obtained at baseline. A stool sample for microbiome analysis will be obtained at all time points. A full list of measures and assessments are listed in table 1.

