j) Parenting (child and parent). A component of the study assessment procedures will include a battery of reliable and valid measures of parenting, including The *Child Report of Parent Behavior Inventory*, the *Comprehensive Feeding Practices Questionnaire*, and The *Consideration of Future Consequences Scale*, *Comprehensive General Parenting Questionnaire*, *Birch Child Feeding Questionnaire*, *Parent Importance Confidence and Readiness Questionnaire*, *Parent Motivation Inventory*, *Family Adaptability and Cohesion Scale IV*.

k) Treatment adherence (child and parent). Adherence to recommendations (e.g. goal setting, stimulus control, contracting) and self-monitoring (% days monitored) for child and parent will be collected using standard study assessment tools to assess treatment adherence. All self-monitoring will be scored for number of days that participant monitored any meals or snacks and for number of days that participants monitored all meals or snacks (as defined by three, time distinct entries for meals and at least one snack). Parents and children will also complete treatment adherence questionnaires that query how many days they self-monitored immediately after meals, how many days they self-monitored at the end of the day, and how accurate they perceive their own self-monitoring to reflect actual intake.

l) Treatment acceptability (child and parent). Questionnaires will assess parent and child liking and any concerns or barriers to implementing the gshFBT or the FBT treatment.

m) Gut microbiome: Participants (parent and child) will be sent a stool collection kit and asked to provide a stool sample within 24 hours of their pre- and post-treatment assessment visits. The BBL CultureSwab will be used to collect samples from subjects (Becton-Dickinson catalog #BD281130) from tissue paper. These swabs have been used successfully by the [name] lab, who has shown that microbiome analysis using these swabs was comparable to that using more traditional stool collection methods. De-identified stool samples will be stored at -20°C. Microbiome analysis will be conducted to examine the relationship between changes in weight and gut microbiome.

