|                                                                 | Attention Bias                                                                           | C,P                | X             | X                    | X                    | X                     |
|                                                                 | Delay Discounting                                                           | C,P                | X             | X                    | X                    | X                     |
|                                                                 | Behavior rating Inventory of Executive Functioning                                       | P,Pc               | X             | X                    | X                    | X                     |
| Biologic
Specimens                                   | Saliva Sample – genetics                                                                 | C, P               | X             |                      |                      |                       |
|                                                                 | Stool Sample - microbiome                                                                | C,P                | X             | X                    | X                    | X                     |
| Treatment
Adherence,
Drop-out,
Acceptability | Attendance (weekly assessment)                                                           | C, P               |               | X                    |                      |                       |
|                                                                 | Habit books (self-monitoring) (weekly assessment)                                        | C, P               |               | X                    |                      |                       |
|                                                                 | Behavioral adherence (developed by team)                                                 | C, P               |               | X                    | X                    | X                     |
|                                                                 | Drop-out rates                                                                           | C, P               |               | X                    | X                    | X                     |

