|                                                                 | Satisfaction survey                                                                      | C, P               |               | X                    |                      |                       |

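### The only scheduled acceptability survey is at post-treatment, with no rating planned when a family leaves, so the hypothesised acceptability difference is likely to be attenuated if dissatisfied families leave FBT more often

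*Protocol*

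**What the plan says.** Secondary aim 1 (Protocol, section 6) covers drop-out, adherence and acceptability. Its hypothesis joins them in one sentence: "families randomized to FBT+PT will have lower drop-out rates, increased program adherence (including attendance, self-monitoring, use of praise), and higher ratings of acceptability".

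The Measures text in section 9, item l, describes the acceptability instruments for child and parent: "Questionnaires will assess parent and child liking and any concerns or barriers" to using the treatment. It gives no timing and mentions no rating at drop-out.

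Table 1 lists one acceptability instrument, "Satisfaction survey", for child and parent, with a single mark in the post-treatment (6-month) column. Other rows in the same block show that data are collected during treatment. Attendance carries a weekly tag, as does the row "Habit books (self-monitoring) (weekly assessment"), and drop-out is recorded at all three later time points.

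For the comparison, the Analysis text states: "These analyses for the Secondary Aim will be conducted using regressions comparing FBT+PT to FBT". Its return-to-baseline rule for missing values is written for primary outcomes and could not serve a rating that has no baseline. The same text defines drop-out as leaving treatment, including families who stop coming without notice. Section 14 adds that children who become frustrated or very stressed may stop and withdraw from the study.

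**The concern.** A family that dislikes a programme is a likely candidate to leave it early. If such families give no rating, the 6-month survey describes mainly those who were content enough to stay. When one arm loses more of them, its remaining mean rises more, and the comparison no longer reflects the arms as randomized.

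The protocol's own hypothesis sets this up. If FBT+PT does retain more families, FBT loses more of its dissatisfied ones, so success on the drop-out part of the aim makes the acceptability part harder to show. An analysis plan can define the analysis set or impute, but it cannot recover ratings that were never collected. Collection timing is fixed in this protocol.

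**Working it through.** The protocol gives no expected difference, SD or power for acceptability, so there is no figure to reproduce. The following is an illustration of size.

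**From the protocol**
- At least 160 dyads randomized (sections 6 and 9).
- Drop-out in such programmes of 20% in academic and 70% in clinical settings (section 7).
- Predicted direction: less drop-out and higher acceptability in FBT+PT (section 6).

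**Assumed**
- 80 families per arm (the allocation ratio is not stated) and two-sided 5% level.
- Ratings Normal with SD 1; true difference 0.5 SD, with 0.3 SD as an alternative.
- The arm-specific drop-out pairs in the table.
- Correlation rho of 0.3, 0.5 or 0.7 between a family's rating and its tendency to stay.
- Families who drop out give no 6-month rating. This is the unfavourable case, not a protocol rule.

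**Formula.** If the fraction d least inclined to stay is lost, then with c = z(d) the mean among those who remain is mu + rho × λ(d), where λ(d) = phi(c)/(1 − d). The observed difference is therefore

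true difference − rho × [λ(d in FBT) − λ(d in FBT+PT)].

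**Values of λ**
- λ(0.10) = 0.1755/0.90 = 0.195
- λ(0.20) = 0.2800/0.80 = 0.350
- λ(0.40) = 0.3863/0.60 = 0.644

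**Worked cases at rho = 0.5, true difference 0.5 SD**
- 20% versus 10%: 0.5 − 0.5 × (0.350 − 0.195) = 0.42 SD
- 40% versus 20%: 0.5 − 0.5 × (0.644 − 0.350) = 0.35 SD

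**Results, true difference 0.5 SD**

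| Drop-out FBT / FBT+PT | rho 0 | rho 0.3 | rho 0.5 | rho 0.7 |
|---|---|---|---|---|
| 20% / 20% | 0.50 | 0.50 | 0.50 | 0.50 |
| 20% / 10% | 0.50 | 0.45 | 0.42 | 0.39 |
| 40% / 20% | 0.50 | 0.41 | 0.35 | 0.29 |
| 70% / 50% | 0.50 | 0.39 | 0.32 | 0.25 |

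With a true difference of 0.3 SD, the 40%/20% row gives 0.21, 0.15 and 0.09 SD for rho of 0.3, 0.5 and 0.7.

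**Power, true difference 0.5 SD.** With ratings from all 160 families it is 88.5%. Some of the fall is only the smaller number of ratings: with rho = 0 it is 83% at 20%/10% and 75% at 40%/20%. Selection lowers it further, to 77–71% and 60–43% respectively, for rho from 0.3 to 0.7.

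**The case against.** The strongest reply is that the missing ratings are inferred. Drop-out is defined as leaving treatment, and nothing restricts the 6-month assessment to completers. That visit is scheduled separately from the sessions, can be held by ZOOM, lets parents complete some surveys by web and is paid. This stands: a reader might infer that the comparison is strictly among families who stayed, and the protocol does not say so. It does not remove the concern, because nothing states that the survey is sought from leavers, some leave without notice, and section 14 allows withdrawal from the study itself.

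A reader might also infer that the difference would vanish or reverse. A simple example seems to show this: rate completers 4.0 and leavers 2.5 in both arms, and completers differ by zero whatever the drop-out. That zero is built in, since treatment is given no effect within either group. Allowing a true effect gives attenuation, and none of the scenarios run, at 0.3 or 0.5 SD, changes sign. At 20%/10% with rho 0.7, reversal would need a true difference below 0.7 × 0.155 = 0.11 SD.

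Two further points have some weight. Table 1 may not be exhaustive: the Measures text speaks of questionnaires in the plural, and the Analysis text mentions therapist ratings that have no row. Therapist ratings do not replace those of families, however. Rating a 20-session programme at its end is also a reasonable choice, and drop-out is tested separately by survival analysis, so a null acceptability result would be read beside it. This limits the damage but leaves the estimate itself attenuated.

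**Conclusion.** The concern holds as likely under-representation of dissatisfied early leavers, with attenuation of the arm difference if leaving is related to dissatisfaction and drop-out is higher in FBT. For an assumed true difference of 0.5 SD, the loss is about 9% to 22% of the effect at 20%/10% drop-out (0.046/0.5 to 0.108/0.5) and 18% to 41% at 40%/20% (0.088/0.5 to 0.206/0.5). These sizes rest on the assumed correlations, on drop-out pairs of which only 20% and 70% are protocol figures (and neither is arm-specific), and on leavers giving no 6-month rating. Any ratings obtained from them would change the size. The bias is zero if leaving is unrelated to acceptability or if the drop-out pattern is alike in both arms.

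The documents do not support saying that the secondary aim would be answered wrongly. One component of one secondary aim is exposed, and the primary outcome is not affected. This is a cheap improvement to data collection.

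**What to change.** - In Table 1 and in the treatment acceptability item of the Measures text, add that the same satisfaction survey is offered to each family when it stops treatment, by web, phone or ZOOM.
- State in the same places that the 6-month survey is sought from every randomized family, whether or not it completed treatment.
- Keep the post-treatment rating as the main comparison, in all randomized families with a rating.
- Add a sensitivity analysis that uses the exit rating for families without a 6-month rating.

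The last available rating should not become the main analysis. It would mix early and end-of-programme ratings, and if drop-out differs by arm the mix would differ too, which exchanges selection for a difference in timing.

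The cost is a few minutes per family for a questionnaire already in use. Some families who leave, especially those who leave without notice, will not answer, so the bias is reduced and not removed.
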